### Strategies to improve adherence to interventions {11c}

We will construct social media groups with teachers to keep in touch.

### Relevant concomitant care permitted or prohibited during the trial {11d}

We will explain the concomitant care and interventions that are prohibited during the trial to the teachers.

### Ancillary and post-trial care {30}

We will provide ancillary and post-trial care at local child mental health outpatient units at the Universidade Federal do Ceará, in Ceará, and UNIFESP in São Paulo.

### Outcomes {12}

Main outcome is as follows: child problems and prosocial behaviours. All outcomes will be measured at the individual level, but analyses will be multilevel based on schools and individuals. The main outcome is a variable compound of three measures (child concentration, disruptive problem and prosocial behaviour) that are measured using only one instrument, the Teacher Observation of Classroom Adaptation-Checklist (TOCA-C). The main outcome measure is completed twice for each child by teachers with mediation of a trained interviewer: at baseline (before trial is implemented) and after trial completion.

### Participant timeline {13}

**Table Tabb:** 

SPIRIT schedule							
Forms and procedures				Study period			
Activity	CRF (Y/N)^a^	Staff	Time to complete (minutes)	− T1	0	T1	T2
Eligibility screen	N	Study coordinator	5	X			
Informed consent	N	Interviewer	5	X			
Baseline randomization	N	Study statistician	5	X			
Allocation	N	Study coordinator	5	X	X		
Teacher training	N	All members	360		X		

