**Assessments**							
Teacher training	N	Interviewer	10		X		X
Bullying	N	Interviewer	15		X		X
Field checklist	N	Trained supervisor	5			X	
Fidelity	N	Trained supervisor	5			X	
Language and math	N	Interviewer	20		X		X
School observation	N	Interviewer	20		X		X
Teachers protocol	N	Interviewer	15		X		X
Game register	N	Trained supervisor	5			X	
SDQ	N	Trained teacher with mediation of a trained interviewer	15		X		X
STRS	N	Trained teacher with mediation of a trained interviewer	15		X		X
TOCA-C	N	Trained teacher with mediation of a trained interviewer	15		X		X

^a^Case report form

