### Concealment mechanism {16b}

Only 30 of the eligible schools will join the trial based on our pre-estimated sample size. The initial selection of 30 schools will use www.random.org. All of the schools’ names will receive a number from one to the total number of eligible schools (i.e., if there are 42 eligible school names, then each one will receive a number from 1 to 42). A random number generator will select 30 numbers from a range of 1 to the total number of eligible schools. These 30 numbers will be randomly assigned to control or intervention groups using Efron’s biased coin to ensure balanced groups. All schools recruited in the same city will be randomized simultaneously. Randomization within each city will be performed when all schools are recruited for that city, rather than waiting until all schools (across all cities) are recruited and then performing randomization of all schools simultaneously. Members of the trial team who are involved with recruitment of schools will be unaware of previous allocations. Trial researchers, not involved with school recruitment, will inform schools of their randomized allocation.

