### Implementation {16c}

All schools from the 30-school lists that give consent for participation and fulfil the inclusion criteria will be randomized. The staff member responsible for the recruitment and baseline interviews will request the randomization. The Ministry of Health team will implement all stages of the intervention, including the recruitment, informing of intervention treatment and supervision.

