## Assignment of interventions: blinding

### Who will be blinded {17a}

Due to the nature of the intervention, neither teacher participants nor school staff can be blinded to the allocation. Data collection team will be blind to which group (control or intervention) the school will be allocated. We will not directly provide information on the school allocation to the external assessors who will interview the teachers, but no one is truly blinded in this type of randomized controlled trial because the teachers may accidentally report the school status.

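### The schedule puts randomisation before the baseline TOCA-C and teacher training in the same period as that rating, and nothing requires unblinded teachers to rate pupils before they know their arm

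*Protocol article*

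**What the plan says.** Participant timeline {13} has four columns: -T1, 0, T1 and T2.

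- "Baseline randomization" is marked at -T1 only.
- Allocation is marked at -T1 and 0.
- The 360-minute "Teacher training" given by all team members is marked at 0.
- TOCA-C, SDQ and STRS are marked at 0 and T2, and the person completing them is given as "Trained teacher with mediation of a trained interviewer".
- The programme itself runs at T1.

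Outcomes {12} times the TOCA-C "at baseline (before trial is implemented) and after trial completion".

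Who will be blinded {17a} states that "neither teacher participants nor school staff can be blinded to the allocation". Of the interviewers it says: "Data collection team will be blind to which group (control or intervention) the school will be allocated".

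On disclosure, Concealment mechanism {16b} says: "Trial researchers, not involved with school recruitment, will inform schools of their randomized allocation". It gives no time for this relative to the baseline ratings.

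Statistical methods for main outcomes {20a} enters the baseline value of each outcome as a predictor of its follow-up value in every case. Other covariates enter only if baseline imbalance is seen.

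**The concern.** Baseline adjustment is safe in a randomised trial because the baseline was fixed before allocation, so any difference between arms in it is chance. That protection is lost if the person giving the score already knows the arm, or has just been trained to watch for rule-breaking. Any shift in scoring that differs between arms then enters the covariate, and the model carries part of it into the treatment effect.

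This matters more here than in many trials. The main outcome has only two measurements, both supplied by the teacher who delivers the programme or works in a control school. The follow-up rating is unavoidably unblinded. The baseline is the one TOCA-C score that could be kept clear of allocation, and the schedule does not secure this. The teacher questionnaires, also at period 0, are exposed in the same way if they are used to choose further covariates.

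**Working it through.** No figure in the plan is in dispute. The check is one of sequence, followed by an illustration of how a shift would carry through.

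**1. Order in the schedule (Participant timeline {13})**

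| Step | -T1 | 0 | T1 | T2 |
|---|---|---|---|---|
| Consent | X | | | |
| Randomisation | X | | | |
| Allocation | X | X | | |
| Elos teacher training (360 min) | | X | | |
| TOCA-C, SDQ, STRS, teacher questionnaire | | X | | X |
| Elos programme | | | X | |

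Randomisation precedes the first TOCA-C. Allocation, training and the first TOCA-C can share period 0, with no order among them.

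**2. Does the text supply the missing order?**

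- Outcomes {12}: a rating before implementation. The programme starts at T1, so a rating made after disclosure and after training still satisfies this.
- Sequence generation {16a}: only the schools' agreement must precede randomisation, not baseline data.
- Concealment mechanism {16b}: schools are told their arm, with no time given. It does randomise all schools of a city at once, after that city's recruitment is complete.
- Implementation {16c}: "The staff member responsible for the recruitment and baseline interviews will request the randomization". This does not say that the interviews are finished first.
- Who will be blinded {17a}: blinding the interviewer does not protect a score that the teacher supplies.

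None of these places the rating before randomisation, disclosure or training.

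**3. How a shift would carry through**

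Input from the protocol: target difference 0.25 (Sample size {14}). Everything else is assumed: a constant shift *b* in the Elos arm's baseline ratings, a slope *β* of follow-up on baseline, and a baseline score that is not centred within classrooms.

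Adjusted effect = (Y_Elos − Y_control) − β × (X_Elos − X_control)

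With a pre-allocation baseline, the second bracket has expectation zero. With a shift *b* it has expectation *b*, so the baseline contributes an error of −β × b. A constant shift leaves the within-arm slope unchanged. Absolute size, and share of 0.25:

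| | β = 0.3 | β = 0.5 | β = 0.7 |
|---|---|---|---|
| b = 0.05 | 0.015 (6%) | 0.025 (10%) | 0.035 (14%) |
| b = 0.10 | 0.030 (12%) | 0.050 (20%) | 0.070 (28%) |
| b = 0.20 | 0.060 (24%) | 0.100 (40%) | 0.140 (56%) |

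**4. Direction**

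Take a problem subscale on which higher is worse, so that a negative error favours Elos. If a fraction *r* of the shift is still present in the follow-up ratings, the net error is r × b − β × b = (r − β) × b. For b = 0.10 and β = 0.5 to 0.7:

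- r = 0 (shift gone by follow-up): −0.05 to −0.07, towards Elos.
- r = 1 (shift fully persists): +0.05 to +0.03, against Elos.
- b = −0.10 reverses both.

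The protocol gives none of *b*, *β* or *r*, so neither size nor sign can be fixed.

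**The case against.** The strongest reply is that randomising is not disclosing. A list held by the statistician cannot affect a teacher's rating; only knowledge of the arm, or the training, can. Allocation is marked at 0 as well as -T1, so schools may be told late in period 0, after the forms are in. Implementation {16c} names recruitment and baseline interviews together and then the request for randomisation, which can be read as interviews first. This stands in part: it is not shown that any teacher knows the arm when rating. But the schedule shows the opposite order to that reading, and no sentence settles the matter.

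Three stronger readings are tempting and are not supported.

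- *The raters are already Elos-trained because the schedule calls them trained teachers.* Control teachers complete the same form. The assessments part of the schedule also has a separate 10-minute teacher training row, given by the interviewer at 0 and T2, which plausibly refers to the forms.
- *The roles conflict, because baseline staff request the randomisation while data collectors are blind.* Requesting an allocation is not learning it. The statistician randomises, researchers outside recruitment tell the schools, and each city is randomised in one step. On this point the sections are compatible.
- *The effect is inflated in favour of Elos, by something like 20% to 28% of the target.* That needs an assumed shift of 0.10, an assumed slope of 0.5 to 0.7, and a shift that vanishes by follow-up. A persistent shift gives a net error the other way.

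**Conclusion.** The point holds as a weakness in sequence. As written, the schedule permits a baseline rated after randomisation, by teachers who may know their arm and may have been trained, to enter the main model as a fixed covariate. Contamination is possible, not demonstrated. Its size and direction cannot be determined from the protocol. The 0.015 to 0.14 range (6% to 56% of the 0.25 target) rests wholly on the assumed shift and slope and shows only that the risk is not negligible.

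Clean sequencing removes the baseline part of the error, −β × b. It does nothing about unblinded rating at follow-up, which is a separate limitation. If the same shift is present at both times the two parts partly cancel, but that would be an accident and no reason to leave the baseline exposed.

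**What to change.** Amend the schedule, Outcomes {12}, Concealment mechanism {16b} and Implementation {16c} to give one order within each city:

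1. consent;
2. all teacher-rated and teacher-completed baseline measures (TOCA-C, SDQ, STRS, teacher questionnaires) in every school of that city;
3. randomisation;
4. disclosure to schools;
5. Elos training.

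If randomisation cannot wait, the minimum is that the baseline forms are complete before any school of that city learns its arm and before Elos training starts.

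The cost is small. Each city is already randomised in a single step, so planned steps are re-ordered without new visits; allocation simply waits for the baseline forms.

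Trial status dates the start of recruitment to March 2019, so baseline may already be collected. In that case, record for each school the dates of baseline rating, disclosure and training. If any ratings followed disclosure, add a sensitivity analysis without baseline adjustment. That analysis is free of the contaminated covariate, but it would usually be less precise and remains open to unblinded rating at follow-up, so it should be read beside the adjusted result and not as a replacement for it.

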**Intervention**							
Elos 2.0 Programme	N	Trained teachers	480–2400			X	
Teacher supervision	N	Trained supervisor	120			X	
Supervisor supervision	N	Study coordinator	240			X	
**Assessments**							
Teacher training	N	Interviewer	10		X		X
Bullying	N	Interviewer	15		X		X
Field checklist	N	Trained supervisor	5			X	
Fidelity	N	Trained supervisor	5			X	
Language and math	N	Interviewer	20		X		X
School observation	N	Interviewer	20		X		X
Teachers protocol	N	Interviewer	15		X		X
Game register	N	Trained supervisor	5			X	
SDQ	N	Trained teacher with mediation of a trained interviewer	15		X		X
STRS	N	Trained teacher with mediation of a trained interviewer	15		X		X
TOCA-C	N	Trained teacher with mediation of a trained interviewer	15		X		X

^a^Case report form

### Sample size {14}

Our target between group mean difference for TOCA scores was 0.25, which we believe to be a plausible treatment effect for this intervention, and would be clinically meaningful. A sample size of *N* = 3000 child participants (1500 in each treatment group), comprising 15 clusters with an average of 100 children per cluster, is sufficient to provide 92% power, with an alpha threshold of 0.05, a standard deviation of 0.80 based on the study by Storr et al. [40], an intraclass correlation coefficient of 0.05 (a conservative value compared with a previously reported value of 0.039 by Liljequist et al. [41]), and setting the coefficient of variation of cluster sizes at 0.70.

### Recruitment {15}

In collaboration with the Municipal and State Departments of Health and Education, we will select schools for inclusion in the study according to the following criteria: (1) being a public school and (2) having at least one class of each grade (first to fourth grade). Each city will have its own list of schools. We will randomly select schools for a specific city from each list, and the eligible schools will be invited to participate in the trial. However, the schools may refuse to participate in the trial. In case of refusal, we will randomly select 10% more schools to replace the schools that refused to participate.

## Assignment of interventions: allocation

### Sequence generation {16a}

The allocation of schools (1:1) to the control or intervention group will be performed via simple random drawing from the list of the Anísio Teixeira National Institute of Educational Studies and Research (INEP, its acronym in Portuguese), which includes all Brazilian schools separated by city. Randomization will be performed using a quantitative methodology in PASS 15 Efron’s biased coin (two treatments, equal sample sizes). The target sample sizes are the same for both groups. To achieve a longitudinal balance between groups, the algorithm dynamically changes the group assignment probabilities.

The unit of randomization between groups is the schools and not the classes. Therefore, there will be no control classes in an experimental school and vice versa to avoid sample contamination. Agreement to participate in the study was received from the schools before randomization.

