## Trial design {8}

A cluster-randomized controlled superiority trial will be performed in 30 schools in three cities (15 controls and 15 in the experimental group), with a total of 3800 children participating in the test (1900 in the control group and 1900 in the intervention group). This study is a randomized controlled trial with two parallel groups (intervention and control) of students aged 6 to 10 years and enrolled in the first to fourth year of elementary education in public schools in the cities of Fortaleza, Eusébio and São Paulo, which are located in the states of Ceará and São Paulo. The ratio of intended numbers of participants in each of the comparison groups is 1:1. The control group receives treatment as usual in Brazil, i.e., no behavioural intervention at the school.

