## Interventions

### Explanation for the choice of comparators {6b}

Among the schools selected to participate in the study, a second simple randomized selection will define the control and experimental schools at a ratio of 1:1 control and experimental schools per municipality. The selected comparison group is treatment as usual, which means no behavioural interventions delivered in the control schools. This is a suitable comparator, as it is the standard experience of schoolchildren in Brazil. Public schools for children in Brazil do not usually receive interventions to improve behavioural skills.

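### Efron's biased coin does not guarantee the stated 15:15 split or 1:1 per municipality, although each city's schools are allocated in one step and a fixed within-city split is available

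*Protocol article*

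**What the plan says.** **The split.** Trial design {8} has the trial "performed in 30 schools in three cities (15 controls and 15 in the experimental group"). The section on the choice of comparators {6b} adds that allocation is "at a ratio of 1:1 control and experimental schools per municipality".

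**The method.** Sequence generation {16a} states: "Randomization will be performed using a quantitative methodology in PASS 15 Efron’s biased coin (two treatments, equal sample sizes"). It continues: "The target sample sizes are the same for both groups", and "To achieve a longitudinal balance between groups, the algorithm dynamically changes the group assignment probabilities". Both {6b} and {16a} also use the word simple for the random selection or drawing. No coin probability is given.

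**The timing.** Concealment mechanism {16b} states: "All schools recruited in the same city will be randomized simultaneously". This happens once recruitment in that city is complete.

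**The draw of schools.** Recruitment {15} gives each city its own list and says: "We will randomly select schools for a specific city from each list". Concealment mechanism {16b} instead says: "A random number generator will select 30 numbers from a range of 1 to the total number of eligible schools". Neither section gives the number of schools per city.

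**The concern.** A biased coin makes assignment to the smaller arm more likely. It does not fix the arm sizes, so the plan states an allocation that its named method does not guarantee. Such a coin is useful when units arrive one at a time. Here all schools of a city are known before any of them is allocated, so a fixed split within the city is available and the coin gains nothing.

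Only 30 units are randomised, in three cities across two states. Chance imbalance of arm by city is therefore plausible, and the design could exclude it. The statistical methods {20a} name no standing term for city.

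The draw of schools adds a second difficulty. If 30 numbers are taken from one list of all eligible schools, the count in each city is left to chance, and a city with an odd count cannot be split 1:1.

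**Working it through.** **Inputs from the article.** 30 schools, 15 per arm, three cities ({8}); 1:1 per municipality ({6b}); Efron's coin ({16a}, {16b}). From the sample size section {14}: difference 0.25, SD 0.80, ICC 0.05, mean cluster size m = 100, coefficient of variation 0.70, alpha 0.05, power 92%. The 15 clusters are read as per arm, since 1500/100 = 15.

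**Assumptions.** Coin probability p from 0.60 to 0.90, and 10 schools per city, because the article gives neither. Alpha is taken as two-sided.

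**1. The plan's own power figure.**
- R = m·ICC/[1+(m−1)·ICC] = 5/5.95 = 0.840.
- Relative efficiency = 1 − CV²·R(1−R) = 1 − 0.49 × 0.840 × 0.160 = 0.934.
- Design effect = 5.95/0.934 = 6.37.
- SE = 0.80·√[6.37 × (1/1500 + 1/1500)] = 0.0737.
- 0.25/0.0737 − 1.96 = 1.43, so power is 92.4% (normal approximation). The stated 92% is reproduced. With t on 28 df it is 90.5%.

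**2. How the coin behaves.** Let D be the difference between arms. If D = 0 the next school is assigned with probability 1/2. Otherwise it goes to the smaller arm with probability p. So |D| moves from 0 to 1 with certainty, and from d > 0 to d−1 with probability p or to d+1 with probability 1−p.
- Two schools: P(1:1) = p.
- Four schools: P(2:2) = p²(2−p), which is 16/27 = 59% at p = 2/3.
- Ten schools, same chain: 53.0% at p = 2/3.
- Long even runs: the limit is (2p−1)/p, which is 50% at p = 2/3 and 89% at p = 0.90.

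Each of these is below 1 whenever p is below 1.

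**3. Results (exact distribution of D).**

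| p | One coin over 30: 15:15 | Coin per city: 15:15 | Coin per city: every city 5:5 | Coin per city: 17:13 or worse |
|---|---|---|---|---|
| 0.60 | 35% | 21% | 7% | 43% |
| 2/3 | 50% | 28% | 15% | 31% |
| 0.75 | 67% | 40% | 30% | 17% |
| 0.90 | 89% | 72% | 70% | 2% |

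The fourth column is the single-city probability cubed, for example 0.530³ = 0.149 at p = 2/3. Other even city splits change little: at p = 2/3, 4/10/16 gives 15:15 in 29% and every city exact in 16%. The unknown p drives the range.

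**4. If the run is forced to end at 15 per arm.** 15:15 is then certain. With 10 schools per city taken in sequence and p = 2/3, every city is 5:5 in about 28% (simulation).

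**5. If the draw is pooled.** Taking 30 from an assumed 42 eligible schools, all three city counts are even, so that exact 1:1 per city is possible, in about 25% of draws. This was nearly the same for the three assumed distributions of the 42 schools over cities that were tried.

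**6. Cost in power (t, 28 df).** 15:15 90.5%; 16:14 90.4%; 17:13 90.0%; 18:12 89.4%; 20:10 87.0%. Relative efficiency at 17:13 is 4 × 17 × 13/30² = 0.982.

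**The case against.** - **The split may be only intended or forced.** The article speaks of target sizes, and the named software option refers to equal sample sizes. If that option forces 15 per arm, 15:15 is met. This stands as an open possibility, because the article does not say. It would not rescue 1:1 per municipality.
- **The probabilities are wide.** They depend on an unstated p, and no single figure should be taken as the chance of balance. This stands, and the range is given for that reason. The conclusion does not depend on p as long as p is below 1.
- **Imbalance costs little and is not bias.** This stands. A reader might infer that the trial would be underpowered or the effect estimate biased. The power figures do not support the first. Chance imbalance under valid randomisation is not the second. The statistical methods {20a} also always include the baseline outcome, and add covariates when baseline differences are moderate or strong.
- **The pooled draw is one reading.** {15} gives each city its own list, {16a} says the national school list is separated by city, and {16b} itself refers to randomisation within each city. A reader might infer that cities will receive odd or very small numbers of schools. That follows only from the pooled reading, which the surrounding text does not clearly support. What stands is that {15} and {16b} do not agree and give no city counts.
- **The word simple may be everyday language.** In {16a} the next sentence names the algorithm, so this is not firm evidence of unrestricted randomisation.

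**Conclusion.** The point holds as a mismatch between a stated property and a named method: the biased coin does not guarantee 15:15 or 1:1 per municipality. It would be too strong to say that the method cannot deliver them, because exact balance can occur by chance and 15:15 would be certain if the software forces it.

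Under the assumed 10/10/10 split and p from 0.60 to 0.90, a coin per city meets 1:1 in every city in about 7% to 70% of randomisations. The consequence is modest: about 0.1 to 1 point of power for 16:14 to 18:12, and an avoidable chance imbalance of arm by city with 30 clusters. The disagreement between {15} and {16b} on the draw of schools needs reconciling in any case. It bears on the split within cities, not on 15:15.

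**What to change.** **If allocation has not been done.**
- In {15} and {16b}, state an even number of schools for each city, adding to 30. Draw them from that city's own list, and fill refusals from the same list before randomisation.
- In {16a}, replace the biased coin and the reference to simple drawing with one random permutation of the consenting schools within each city, half to each arm, generated once that city's recruitment is complete. Align {6b} with this.
- State that an odd count can be split only to within one school. Note also that the replacement of intervention schools described in {11b} can change the split under any algorithm if it happens after allocation.

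With even counts this gives 1:1 in every city and 15:15 overall. It needs no extra schools, and concealment is not weakened, because each city is still allocated in one step.

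**If allocation has been done**, which is possible because the article dates the start of recruitment to March 2019, do not reword the method. Report the method actually used, including the coin probability and whether arm sizes were forced, and the schools per arm in each city. Correct the 15:15 and 1:1 per municipality statements if they were not met. The cost is a clarification in the text.
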